#### Primary outcome

The primary outcome will be performance of activities of daily living and satisfaction with that performance, measured by the COPM
[12]. During a semi-structured interview, the participant will be encouraged to identify problems with their self-care, productivity and leisure activities. The participant will thereafter rate importance of each identified activity on a 1 to 10-point scale, before the five most important activities are rated for performance and satisfaction with performance, again on 1 to 10-point scales (higher scores reflect higher importance, better performance or higher satisfaction). A change of two points is regarded as a clinically relevant improvement or deterioration
[12].

A literature review based on 19 methodological studies
[13], concludes that COPM is a valid, reliable, clinically useful and responsive outcome measure. The Norwegian version of COPM has been tested for validity and responsiveness
[14] and reliability
[15] in persons with rheumatic diseases with good results. Psychometric properties have also been found satisfactory in elderly persons with a variety of diagnoses
[14, 16, 17].

#### Secondary outcomes

Functional mobility will be measured using the Timed Up and Go (TUG) Test, which was developed as a short test of basic mobility skills in frail community-dwelling elderly persons
[18]. The participant will be encouraged to walk fast without compromising safety. The time taken to rise from a chair with arm rests, walk 3 m, cross a line on the floor, turn, walk back, and sit down again will be registered. Normative data for home-dwelling older adults exists
[19]. Test-retest reliability
[19] and intrarater reliability
[18] in community-dwelling elderly people has been found to be excellent and moderate, respectively. Criterion validity
[18] and construct validity
[20] has also been found to be excellent and moderate, respectively, in a community-dwelling older population.

Grip strength will be measured with the hydraulic instrument, Jamar Dynamometer. The participant will sit in front of a table holding the dynamometer. With the elbow at 90 degrees flection, the participant will be asked to grip and squeeze the dynamometer as hard as possible. Both hands will be tested twice. The mean of the two assessments will be calculated. Normative values for average grip strength in an elderly population are available
[21]. The instrument has been tested for criterion validity in a normal population
[22] and test-retest reliability in community-dwelling older adults
[23] with excellent results.

Health-related quality of life will be measured by the COOP/Wonka, which is a generic, self-reported outcome measure
[24]. The chosen revised version
[25] consists of six questions with associated drawings, where each question represents a separate domain. The responses are scored on a five-point ordinal scale ranging from 1 to 5 (1 = best, 5 = worst). In a structured review, COOP/Wonka was found to have weak evidence of reliability, adequate evidence of validity, and good evidence of responsiveness in an elderly population
[26].

### Sample size calculation

In an earlier study performed on older adults, the standard deviation for the primary outcome has been shown to be 1.4 for COPM performance and 1.6 for COPM satisfaction
[27]. With a conservative estimate of the standard deviation of 2.5, sample size calculations showed that 21 participants need to be included in each group to detect a change of 2 points as statistically significant (with a two-sided 5% level and a power of 80%)
[28]. We also assumed a within-subject correlation coefficient for the three follow-up measurements of 0.7. To take into account the possibility of a relatively high dropout rate (up to 40%) due to frail participants, 60 participants (30 people in each group) will be included.

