**Secondary outcome measures**		
Lower extremity function and mobility	Timed Up and Go, measured in seconds, the second of two trials will be used	t1, t2, t3
Grip strength	Jamar dynamometer, measured in kilograms, the mean of two trials will be used	t1, t2, t3
Health-related quality of life	COOP/Wonka. Scale 1–5, 1 is low health-related quality of life	t1, t2, t3

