#### Analysis of effectiveness

Outcome measures will be compared between the treatment groups at the 3 and 9 month follow-ups using linear mixed-effects models with adjustment for baseline measurements
[29]. The mixed-effects model approach (also called random coefficient model or multilevel model) will be used to account for correlated data introduced by the repeated measures study design, due to its versatility in the modelling of the time factor and in allowing varying numbers of measurements per individual. In the analyses, group and time by group interaction will be entered as fixed factors, time as a repeated factor and participant as a random factor. In the case of group imbalance in the distribution of gender or other baseline characteristics, these variables will be included in the model. Models will be fitted with random intercepts and also with random slopes. Robustness and underlying assumptions will be investigated. Estimated regression coefficients will be presented with 95% confidence intervals and p-values.

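### Dropout is attributed to frailty, but the COPM model admits baseline frailty markers only on baseline imbalance, so dropout that differs by arm could bias the group difference

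*Protocol article*

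**What the plan says.** In the protocol article, Sample size calculation raises the target from 21 to 30 per group to allow for "the possibility of a relatively high dropout rate (up to 40%) due to frail participants". Frailty is the only reason given for loss.

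Analysis of effectiveness compares the groups at 3 and 9 months with a linear mixed model adjusted for baseline measurements. Group and time by group are fixed factors, time is a repeated factor and participant is random. One stated merit of the model lies "in allowing varying numbers of measurements per individual". Gender or other baseline characteristics are added if the groups prove imbalanced on them. Robustness and assumptions are to be examined, but no method is named.

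Table 2 lists Timed Up and Go and grip strength ("Jamar dynamometer, measured in kilograms, the mean of two trials will be used") at baseline, 3 and 9 months, and comorbidity and age are also recorded at baseline. The Secondary outcomes text describes Timed Up and Go as a mobility test developed for frail older people living at home. None of these is a pre-specified covariate in the COPM models.

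**The concern.** A likelihood-based mixed model copes with unequal numbers of measurements if, given what is in the model, dropout is unrelated to the unseen values. The article names frailty as the likely cause of loss. Its covariate rule, however, looks at balance at randomisation, whereas the problem would arise later. A frailty marker that is balanced at baseline stays out, even if the people who remain come to differ in frailty between the arms.

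Such divergence is plausible from the article's own description. Reablement involves daily training, repeated practice and at least one therapist hour a week. Standard treatment is for most people compensating help. Participants know their arm, and controls are promised reablement after 9 months. If frail people leave reablement more readily than standard care, those remaining in reablement are fitter and part of that difference is counted as benefit. The reverse pattern would hide benefit.

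**Working it through.** **1. The plan's own figures.** Inputs from Sample size calculation: "With a conservative estimate of the standard deviation of 2.5", a 2-point difference, "with a two-sided 5% level and a power of 80"%, and a "within-subject correlation coefficient for the three follow-up measurements of 0.7".

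- Single measurement: n = 2 × [2.5 × (1.960 + 0.842) / 2]² = 24.5 per group.
- Factor for the mean of k follow-ups: (1 + (k − 1) × 0.7) / k. For k = 2 it is 0.85, and 24.53 × 0.85 = 20.85, so 21. For k = 3 it is 0.80, giving 19.6, so 20. The stated 21 is reproduced with two follow-ups.
- 21 × 1.4 = 29.4, so 30 per group and 60 in all. After 40% loss, 30 × 0.6 = 18 per group remain. How the inflation was done is a separate matter.

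**2. When does frailty-driven dropout bias the difference?** Approximately, bias = γ × Δ. Here γ is the fall in follow-up COPM per SD of frailty at a fixed baseline COPM, and Δ is how much less frail, in SDs, the remaining reablement participants are than the remaining controls at the same baseline COPM. If frailty acts on dropout equally and the rates are equal, Δ = 0 and there is no bias.

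**3. Size of γ.** From the article: SD 2.5 and correlation 0.7, here also applied between baseline and follow-up. Assumed: frailty correlates 0.3 (negatively) with baseline COPM, and follow-up COPM falls b points per SD of frailty.

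γ = 2.5 × (b/2.5 − 0.7 × 0.3) / (1 − 0.3²)

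- b = 0.75: 2.5 × 0.09 / 0.91 = 0.25
- b = 1.0: 2.5 × 0.19 / 0.91 = 0.52
- b = 1.5: 2.5 × 0.39 / 0.91 = 1.07

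**4. Simulated bias in COPM points.** A positive value favours reablement. Everyone lost has no follow-up COPM. The model adjusts for baseline COPM only. Slopes are log-odds of dropout per SD of frailty. Dropout is 40% in each arm unless stated.

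| Dropout pattern | b = 0.75 | b = 1.0 | b = 1.5 |
|---|---|---|---|
| Same slope (1) and rate in both arms | −0.01 | 0.00 | 0.00 |
| Frailty-driven in reablement only, slope 1 | 0.07 | 0.16 | 0.32 |
| Frailty-driven in reablement only, slope 2 | 0.11 | 0.24 | 0.49 |
| Frailty-driven in control only, slope 1 | −0.07 | −0.16 | −0.32 |
| Same slope (1), 40% reablement, 20% control | 0.02 | 0.08 | 0.16 |
| Same slope (1), 30% reablement, 50% control | −0.05 | −0.08 | −0.15 |

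The second row agrees with the formula: 0.072/0.247, 0.161/0.522 and 0.322/1.071 are all about 0.3, so Δ is about 0.3 SD. Opposite slopes in the two arms give 0.16 to 0.65, but require frail people to be the ones who stay in one arm.

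**5. Using the 3-month COPM.** The planned model also uses the 3-month value of anyone lost after that visit. With two follow-ups, dropout of 40% in reablement and 30% in control, and (assumed) half of the losses after 3 months:

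| Partial correlation of frailty with COPM | Slopes, reablement / control | Bias at 3 months | Bias at 9 months |
|---|---|---|---|
| 0.3 | 2 / 0 | 0.08 | 0.19 |
| 0.3 | 2 / 1.5 | 0.04 | 0.07 |
| 0.5 | 2 / 0 | 0.16 | 0.34 |
| 0.5 | 2 / 1.5 | 0.04 | 0.09 |

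The standard error is about 0.5 to 0.57. With an SD of 1.5, close to the 1.4 and 1.6 that the article cites from an earlier study, and a partial correlation of 0.3, the bias is at most 0.12.

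**6. What a covariate achieves.** Adding the exact variable that drives dropout brings the bias to about zero in every pattern in step 4. A proxy that captures half of frailty's variance removes only about half. If the treatment effect itself falls by 0.5 points per SD of frailty, with equal dropout in both arms and b = 1.0, the shift is 0.19 with or without a main-effect covariate.

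**The case against.** The strongest reply is that nothing in the article is contradictory. The 40% is an upper planning allowance, not a forecast of a missingness mechanism, and no rate is given by arm. A reader might infer that heavy frailty-driven dropout by itself biases the primary result. It does not: with the same mechanism and rate in both arms the bias is about zero. That part of the reply stands, and the point is conditional on dropout differing between arms.

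A reader might also infer that the model conditions on nothing but baseline COPM. That is too strong. Imbalanced baseline characteristics can enter, and 3-month COPM informs the 9-month comparison for those lost in between. This lowers the figures in step 4 to those in step 5. It helps less with losses caused by the demands of reablement, which lasts at most 3 months, because those would tend to occur before the first follow-up.

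Larger figures can be produced. A one-follow-up, completers-only simulation with a baseline correlation of 0.5 gives a bias of about 0.3 (type I error 6–7%) at a partial correlation of 0.3, and 0.5–0.6 (9–12%) at 0.5. It combines frailty-driven dropout in reablement with random dropout in controls and has no 3-month value to draw on, so it is an upper end and not a description of the planned model.

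Finally, missing-data sensitivity analyses and the recording of reasons for leaving may sit in the full protocol or analysis plan, which are not shown. Their absence is not counted here. The covariate rule is different: the article states it, and an analysis plan that follows it would leave the frailty markers out unless they happened to be imbalanced.

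**Conclusion.** The point holds in a limited form. The article gives frailty as the reason for possible heavy loss, collects markers of it at baseline, and then ties their use to a trigger unrelated to dropout. If frailty-related dropout differs by arm, the bias is roughly 0.05 to 0.3 COPM points, reaching about 0.5 in strong one-arm scenarios. Against the 2-point target that is about 3% to 15% (0.05/2 and 0.3/2), and about 25% at the extreme. Its direction is unknown.

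These sizes rest on assumed frailty–COPM correlations, dropout slopes and arm-specific rates, none of which the article gives. COPM rates activities that participants choose themselves, so a strong link with grip strength or walking speed should not be taken for granted. The documents do not show that the primary result will be biased. They show a covariate rule that leaves an avoidable exposure, and data already being collected can reduce it at little cost.

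**What to change.** In Analysis of effectiveness, pre-specify baseline Timed Up and Go and baseline grip strength as fixed covariates in both COPM models (performance and satisfaction) for all participants, whether or not they are imbalanced. For these two variables this replaces the imbalance-triggered rule. Timed Up and Go is included because it is the measure the article itself links to frailty. Since both hands are tested, state which grip value is used.

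The cost is about two degrees of freedom, a change of wording and no new data. If the markers are only weakly prognostic, precision falls slightly. If they are prognostic it improves: in the one-follow-up simulation the standard error fell from 0.72 to 0.66 at a partial correlation of 0.5. As imperfect proxies they reduce the bias without removing it, and they do not correct a shift that arises if frailty modifies the treatment effect. The report should not present the adjustment as making the result robust to dropout.

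### Thirty per group does not cover 40% dropout: it leaves 18 per group, not the required 21, and keeps 21 only up to 30% dropout

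*Protocol article*

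**What the plan says.** All the figures stand in one paragraph of the protocol article, Sample size calculation.

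- Required size: "21 participants need to be included in each group to detect a change of 2 points as statistically significant", at a two-sided 5% level and 80% power.
- Planning value: "With a conservative estimate of the standard deviation of 2.5". An earlier study in older adults is cited with standard deviations of "1.4 for COPM performance and 1.6 for COPM satisfaction".
- Repeated measures: "We also assumed a within-subject correlation coefficient for the three follow-up measurements of 0.7".
- Dropout: to allow for "a relatively high dropout rate (up to 40%) due to frail participants, 60 participants (30 people in each group) will be included".

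The Abstract repeats the total of 60. No formula is given for the dropout step, and no other section changes it.

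On the number of follow-ups, Study design and setting has both groups assessed at baseline, 3 and 9 months, with a 15-month assessment in the intervention group only. Table 2 lists the COPM at baseline, 3 and 9 months. Analysis of effectiveness compares the groups at 3 and 9 months.

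**The concern.** A dropout allowance should leave the required number after the stated loss. Here the required number, the loss and the enrolment are all given, and the third does not follow from the first two. The section therefore claims a protection that the design does not have.

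What is at stake is how a null result would be read. The protocol expects frail participants and names 40% as a loss it has allowed for. If that loss occurred, a reader would take the planned 80% power as preserved when, on the protocol's own planning values, it would not be.

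A smaller matter in the same paragraph is the reference to three follow-ups. Only two of the follow-up times are shared by both groups, so the basis of the figure 21 is unclear.

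**Working it through.** **Inputs**, all from Sample size calculation: difference Δ = 2 points; SD = 2.5; two-sided 5% level (1.960); power 80% (0.842); correlation ρ = 0.7; required n = 21 per group; enrolment 30 per group; dropout up to 40%. The article does not show its formula, so the averaging of measurements in step 1 is an assumption.

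**1. Reproducing 21 per group**

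One measurement: n = 2 × (1.960 + 0.842)² × SD² / Δ² = 2 × (2.802)² × 2.5² / 2² = 24.53, so 25.

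For the mean of T measurements with common correlation ρ, the variance is multiplied by [1 + (T − 1)ρ] / T:

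- T = 2: (1 + 0.7)/2 = 0.85, and 24.53 × 0.85 = 20.85, so 21. The t-distribution gives 22.
- T = 3: (1 + 1.4)/3 = 0.80, and 24.53 × 0.80 = 19.62, so 20. The t-distribution gives 21.

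The figure 21 therefore reproduces with two measurements by the normal formula and with three by the t-distribution. The document does not say which was used.

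**2. The dropout step**

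- Left after 40% loss: 30 × 0.60 = 18 per group, below 21.
- Enrolment needed to keep 21: 21 / (1 − 0.40) = 35 per group, 70 in total.
- Largest loss at which 30 per group keeps 21: 1 − 21/30 = 30%.
- For comparison, 21 × 1.4 = 29.4, which rounds up to 30.

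The gap is 35 − 30 = 5 per group, or 10 in total, which is more than rounding can explain.

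**3. Power at 21 and at 18 per group**

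Normal approximation: power = Φ(Δ / [SD_T × √(2/n)] − 1.960), where SD_T = 2.5 × √0.85 = 2.305 for T = 2 and 2.5 × √0.80 = 2.236 for T = 3. For example, with T = 2 and n = 18: 2.305 × √(2/18) = 0.768; 2/0.768 − 1.960 = 0.643; Φ = 0.740. The t figures use the noncentral t-distribution with 2n − 2 degrees of freedom.

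| Measurements averaged | n = 21, normal | n = 21, t | n = 18, normal | n = 18, t |
|---|---|---|---|---|
| Two | 80.3% | 78.3% | 74.0% | 71.5% |
| Three | 82.6% | 80.7% | 76.5% | 74.1% |

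**4. Detectable difference at 80% power** (two measurements, normal): 2.802 × 2.305 × √(2/n) gives 1.99 points at n = 21 and 2.15 points at n = 18. The protocol's Primary outcome section treats 2 points as clinically relevant.

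**The case against.** **The planning SD is cautious.** This is true. At the earlier study's values, with a single follow-up and 18 per group, t-based power is 98.6% for SD 1.4 and 95.4% for SD 1.6. This limits the practical consequence. But 21 was derived from 2.5, and the dropout allowance is stated on top of that 21, so it has to be right on that basis.

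**The planned analysis is more efficient than the calculation.** Analysis of effectiveness adjusts for baseline and uses a mixed model that accepts different numbers of measurements per person, so people lost after 3 months still contribute. This also stands. The correlation between baseline and follow-up is not given. If it were zero, adjustment would add nothing and the figures above would apply; if it were also 0.7 (an assumption), t-based power at 18 per group would be about 90% with one follow-up and 97% with two. The sample size section does not rely on this gain, and the gain does not make 18 equal to 21.

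**Forty per cent might mean adding 40% to 21.** That would give 29.4, so 30, and may be how the figure arose, though this is inference because no formula is shown. A dropout rate is a share of those enrolled, and a loss of 9 out of 30 is 30%.

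**Stronger readings that the document does not support.**

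- A reader might infer that 21 fits only two averaged follow-ups, so that the word three must be an error for two. Step 1 shows that 21 also fits three measurements by the t-distribution. The phrase might mean the three COPM assessments, including baseline.
- A reader might compute power for a single follow-up without baseline adjustment, which gives 67.0% (normal) or 64.5% (t) at 18 per group. That ignores both the repeated measures and the baseline adjustment that the protocol plans, so it does not describe this trial.

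**Conclusion.** The dropout statement is wrong as written. Thirty per group keeps the stated 21 only up to 30% dropout. At 40% it leaves 18, and covering 40% would take 35 per group.

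The shortfall is modest. At the upper limit of the stated dropout range, power is about 72-77% instead of 80%. This rests on SD 2.5, a 2-point difference, correlation 0.7, two or three averaged measurements, complete data only and no baseline adjustment. A reader might conclude that the trial as a whole is underpowered. The document does not support that, since a smaller SD, baseline adjustment or partial data could each raise power. The error lies in the claimed dropout tolerance and leaves the design and analysis otherwise intact.

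The mismatch over the number of follow-ups is a separate point of clarity. It has no bearing on the dropout arithmetic, because 21 is the document's own figure and fits either count.

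**What to change.** Keep 60 participants and restate the allowance, for example: *30 per group retains the required 21 per group for dropout of up to 30%; at 40% dropout 18 per group remain and power is about 72-77%.* It is safer to speak of retaining 21 than of retaining 80% power, because t-based power at 21 with two measurements is 78.3%.

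Separately, reconcile the "within-subject correlation coefficient for the three follow-up measurements of 0.7" with the two follow-ups at which the groups are compared (3 and 9 months) by stating how many measurements the calculation used and which they were. Only those who made the calculation can supply this; changing three to two without checking could misdescribe it.

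The cost is two sentences of text and a less favourable stated dropout tolerance, with no extra participants and no change to the analysis. If the 40% tolerance is to be kept, the alternative is 35 per group (70 in total), which is 10 more participants.

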### Statistical analysis

A bio-statistician blinded to group allocation will monitor the data analysis. The intention-to-treat principle will be followed.

#### Descriptive statistics

Descriptive statistics of baseline characteristics, and of outcome measures at all time-points, will be presented for each group. Mean (standard deviation), median values (inter-quartile range), or number and percentages will be reported.

#### Analysis of effectiveness

Outcome measures will be compared between the treatment groups at the 3 and 9 month follow-ups using linear mixed-effects models with adjustment for baseline measurements
[29]. The mixed-effects model approach (also called random coefficient model or multilevel model) will be used to account for correlated data introduced by the repeated measures study design, due to its versatility in the modelling of the time factor and in allowing varying numbers of measurements per individual. In the analyses, group and time by group interaction will be entered as fixed factors, time as a repeated factor and participant as a random factor. In the case of group imbalance in the distribution of gender or other baseline characteristics, these variables will be included in the model. Models will be fitted with random intercepts and also with random slopes. Robustness and underlying assumptions will be investigated. Estimated regression coefficients will be presented with 95% confidence intervals and p-values.

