**Primary outcome measures**		
Activity performance	Canadian Occupational Performance Measure. Scale 1–10, 1 is low performance	t1, t2, t3
Satisfaction with activity performance	Canadian Occupational Performance Measure. Scale 1–10, 1 is low satisfaction	t1, t2, t3

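### The primary mixed model is not fixed in advance: covariates enter only on observed imbalance, and a random-slope model that two follow-ups cannot identify in its usual form is fitted without naming a primary version

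*Protocol article*

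**What the plan says.** All of this stands in the protocol article, under Analysis of effectiveness.

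- Response times: "Outcome measures will be compared between the treatment groups at the 3 and 9 month follow-ups".
- Role of baseline: the comparison is made "using linear mixed-effects models with adjustment for baseline measurements". The baseline value of the outcome is thus a covariate in every model.
- Terms: "group and time by group interaction will be entered as fixed factors, time as a repeated factor and participant as a random factor".
- Further covariates: "In the case of group imbalance in the distribution of gender or other baseline characteristics, these variables will be included in the model". Neither the candidate variables nor the degree of imbalance that counts is stated.
- Random effects: "Models will be fitted with random intercepts and also with random slopes". Neither version is named as primary, and no rule for choosing is given.

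Table 2 schedules both primary COPM scores at baseline, 3 months and 9 months only, so each participant has two post-baseline values.

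**The concern.** These are rules the article states, not detail left to an analysis plan.

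First, the covariate rule uses the wrong criterion. Allocation is random, so a baseline difference between groups is chance and says nothing about whether the variable predicts outcome. A covariate earns its place by predicting outcome. Under this rule the content of the primary model is unknown until the baseline data have been compared by group, and a prognostic variable that happens to be balanced is left out.

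Second, two random-effects models are to be fitted and either could supply the primary p-value. In its usual form, one of them asks more of two measurements per person than they can give.

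At stake are some precision in a trial of 60 people, and a single primary result that can be identified before the data are seen.

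**Working it through.** **1. The plan's own sample size, and how many follow-ups it implies.** Inputs from Sample size calculation: difference 2, SD 2.5, two-sided 5%, power 80%, within-person correlation 0.7. The stated result is that "21 participants need to be included in each group to detect a change of 2 points as statistically significant".

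- One measurement: n = 2 × [2.5 × (1.960 + 0.842) / 2]² = 24.53 per group.
- Mean of m measurements: multiply by (1 + (m − 1) × 0.7) / m.
- m = 2: 24.53 × 0.85 = 20.85, so 21, the stated figure.
- m = 3: 24.53 × 0.80 = 19.62, so 20.

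The figure of 21 matches two follow-ups, although that section speaks of three. It uses no covariate and no random slope, so nothing below changes it.

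**2. How often the covariate rule would act.** Table 2 lists 12 participant characteristics at baseline under other measures. Assume, for illustration only, that imbalance means p < 0.05 and that the variables are independent. The chance that at least one is flagged is 1 − 0.95¹² = 46%. For 5 variables it is 23% and for 10 it is 40%. At p < 0.10 the figures for 5 and 10 are 41% and 65%. The protocol states no such test, so these show only that the rule would act often.

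**3. What the rule costs.** Simulation with 21 per group and an effect of 2 / 2.5 = 0.8 SD on a single outcome. Covariate correlations with outcome are assumed.

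| Three covariates at 0.3 | Type I error | Power |
|---|---|---|
| No covariates | about 5% | about 72% |
| Triggered at p < 0.05 | 4.4% | 71% |
| Triggered at p < 0.2 | 4.0% | 74% |
| Always adjusted | about 5% | about 81% |

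Always adjusting gains about 81 − 72 = 9 points over no covariates, and 7 to 10 over the triggered rule. With two covariates at 0.2 the gain is 1–2 points. Power levels lie below the planned 80% because the simulation omits the 0.85 factor from step 1; the differences are what matter. With five prognostic covariates, 18 or 30 per arm and a trigger at p < 0.10, the rule's type I error was 2.3–4.1%, so the direction is again conservative.

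**4. Identifiability of the random-slope model.** Let the random intercept have variance a, the slope variance c, their covariance b, and the residual variance s. With responses at 3 and 9 months:

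- Var(3) = a + 6b + 9c + s
- Var(9) = a + 18b + 81c + s
- Cov(3, 9) = a + 12b + 27c

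That is three equations in four unknowns (rank 3). Changing (a, b, c, s) by (45, −6, 1, −18) times any constant leaves all three unchanged:

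- 45 − 36 + 9 − 18 = 0
- 45 − 108 + 81 − 18 = 0
- 45 − 72 + 27 = 0

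The four components therefore have no unique solution. If b is set to 0 there are three unknowns and rank 3: just identified. A random intercept plus residual has two unknowns and is identified. If baseline were a response as well (0, 3 and 9 months), four parameters would face six terms with rank 4: identified.

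**The case against.** **The most important covariate is already fixed.** The baseline value of the outcome is in every model. This stands: only the additional covariates depend on the data.

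**The rule does no harm to error rates.** A reader might infer that data-dependent covariate choice inflates type I error. Applied as written, it does not; it is nominal to slightly conservative. Rates of 8.7–9.8% appear only if the most favourable of the unadjusted, fully adjusted and triggered models is reported, and the protocol plans no such selection. Against a model with no extra covariates, the rule also costs essentially no power. The loss is relative to pre-specified adjustment.

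**The larger gain rests on favourable assumptions.** This stands. The documents give no correlation of any covariate with COPM. For two covariates such as age and gender, the 1–2 point case is the closer guide.

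**Random slopes can be made identifiable.** This is true for a slope independent of the intercept (only just), or with baseline as a response. The section describes baseline as an adjustment, and the random-intercept version is identified either way, so a valid analysis remains. Fitting both versions is not in itself data-dependent; the gap is that neither is primary.

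**Is a time main effect missing?** A reader might infer this from the listed fixed terms and expect biased group differences. The wording does not support it. Group and time-by-group are entered as factors, and these two terms already fit all four group-by-visit means (rank 4), so a common change over time causes no bias.

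**Conclusion.** The point holds in a limited form. The covariate rule makes the primary model depend on the baseline data and selects variables by a criterion unrelated to their value. It leaves type I error at about 4–5% in the main scenarios and gives up between 1–2 and about 9 power points against pre-specified adjustment, depending on the assumed correlations. The random-slope model in its usual form (correlated intercept and slope, free residual) is not identified from the 3- and 9-month responses with baseline as covariate; this follows from the algebra and needs no assumption about the data. With neither version named as primary, the primary result is not uniquely defined. The documents do not support a claim of inflated false positives or of a biased treatment effect.

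**What to change.** In Analysis of effectiveness:

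- Replace the imbalance sentence with a short list of covariates used in every model whatever the observed balance: the baseline value of the outcome (already planned) plus, for example, age and gender. Choose them for expected association with outcome.
- Drop the random-slope model. Name one identified structure for the 3- and 9-month values as primary, either a random intercept or an unstructured 2×2 covariance, and label any other as a sensitivity analysis.

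The cost is a change of wording and one degree of freedom per added covariate. Age and gender are already collected at baseline, and the 21 per group is unaffected.
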